## Abstract

**Background:** Remimazolam, a new ultrashort-acting benzodiazepine, is becoming increasingly applied in general anesthesia. This study is designed to investigate the effect of remimazolam-based total intravenous anesthesia and sevoflurane-based inhalation anesthesia on emergence delirium in pediatric tonsillectomy and adenoidectomy.

**Methods and analysis:** This is a monocentric, prospective, randomized, double-blind clinical trial. A total of 90 pediatric patients will be randomized to receive remimazolam-based total intravenous anesthesia (remimazolam group, n = 45) or sevoflurane-based inhalation anesthesia (sevoflurane group, n = 45). The primary outcome will be the incidence of emergence delirium, which will be evaluated using the Pediatric Anesthesia Emergence Delirium (PAED) scale. The secondary outcomes include the extubation time, recovery time, behavior change using the post-hospitalization behavior questionnaire for ambulatory surgery (PHBQ-AS), and adverse events.

**Ethics and dissemination:** This study has been approved by the Institutional Review Board (IRB) of the Second Affiliated Hospital and Yuying Children’s Hospital of Wenzhou Medical University (2023-K-262-02).

**Clinical trial registration:**
ClinicalTrials.gov, identifier NCT06214117.

## Background

Emergence delirium (ED) is defined as a combative, excited, and disoriented behavior that requires transient restraint during emergence from anesthesia. This phenomenon represents a frequent complication in children undergoing general anesthesia, with an incidence from 10% to 20% in general (Malarbi et al., 2011; Doerrfuss et al., 2019). The prevalence of ED is associated with several factors, including the use of volatile anesthetics, type of surgery, age, preoperative anxiety, pre-existing behavior, and patient and parent interaction with healthcare providers (Mason, 2017). In preschool-aged children undergoing tonsillectomy and adenoidectomy with sevoflurane anesthesia, the incidence of emergence delirium (ED) has increased significantly, reaching up to 40%–60% (El-Hamid and Yassin, 2017; Yang et al., 2022).

Although ED in children is mostly self-limited, the presence of ED can not only delay recover and increase healthcare costs but may also decrease parent satisfaction scores with anesthesia (Mason, 2017). Unfortunately, the etiology and pathogenesis of ED is not completely understood, and effective pharmacological interventions to treat this condition are lacking (Tripp et al., 2021; Sobol and Sobol, 2022).

Sevoflurane-based inhalational anesthesia is widely used in pediatric tonsillectomy and adenoidectomy due to its rapid onset, quick emergence, and minimal airway irritation (Yang et al., 2022). However, this approach is accompanied not only with a high incidence of emergence delirium but also with concerns regarding environmental pollution and the exposure of healthcare personnel to inhalational anesthetics (Miyabe-Nishiwaki et al., 2021). The adoption of total intravenous anesthesia (TIVA) can avoid these issues and is becoming a routine in clinical practice (Chandler et al., 2013; Jo et al., 2019). Propofol is the most common intravenous anesthetic drug, preferred for its rapid onset and short duration of action. Previous studies have demonstrated that propofol-based TIVA is associated with a lower incidence of emergence delirium compared to sevoflurane-based inhalational anesthesia (Chandler et al., 2013). Despite its benefits, propofol has various side effects, including pain during injection, addiction, respiratory depression, and propofol-related infusion syndrome (PRIS) (Chen et al., 2022). These drawbacks limit its further application in pediatric patients.

Remimazolam, a new ultrashort-acting benzodiazepine, is becoming increasingly applied in general anesthesia. Compared to propofol, remimazolam exhibits favorable characteristics such as no injection pain, metabolism independent of liver and kidney function, and minimal respiratory depression (Zhao et al., 2023). These attributes make remimazolam particularly well-suited for pediatric patients. The pharmacokinetics and pharmacodynamics of drugs are different in children compared to adults due to the physiological maturation and development of various organs, transporter, and enzyme systems (Rodieux et al., 2022). Despite this, the majority of available research has been conducted in adults, and data on the pediatric population are scarce (Yang et al., 2022; Fang et al., 2023; Gao et al., 2023). Recently, a clinical trial has garnered considerable attention for demonstrating that a single intravenous injection of remimazolam before the end of surgery can significantly reduce emergence delirium in children (Yang et al., 2022). However, research into the efficacy of remimazolam-based TIVA in reducing the incidence of emergence delirium among pediatric patients remains limited. Therefore, this study is designed to compare the occurrence of emergence delirium in children who undergo tonsillectomy and adenoidectomy under remimazolam-based TIVA or sevoflurane-based inhalational anesthesia.

## Materials and methods

### Study design

This is a monocentric, prospective, randomized, double-blind study and will be conducted at the Second Affiliated Hospital and Yuying Children’s Hospital of Wenzhou Medical University. A total of 90 pediatric patients will be randomly assigned to two groups: remimazolam group or sevoflurane group. The consort flow diagram and time frame are shown in Figures 1, 2, respectively.

**FIGURE 1 F1:**
[figure not shown]
Consort flow diagram.

**FIGURE 2 F2:**
[figure not shown]
Time frame.

The study protocol has been approved by the Institutional Review Board (IRB) of the Second Affiliated Hospital and Yuying Children’s Hospital of Wenzhou Medical University (2023-K-262-02) and registered at ClinicalTrials.gov (NCT06214117, 18 January 2024). The trial will be conducted in compliance with the study protocol, the Declaration of Helsinki, and good clinical practice (GCP).

### Eligibility criteria

#### Inclusion criteria

1) Age 3–6 years;2) American Society of Anesthesiologists (ASA) I or II;3) Booked for tonsillectomy and adenoidectomy;4) Body mass index (BMI) for age between the 25th and 85th percentiles according to the 2000 Centers for Disease Control and Prevention (CDC) growth charts (Kuczmarski et al., 2002).

#### Exclusion criteria

1) Children (ASA III or IV) who have abnormal liver and kidney function, cardiovascular dysfunction, endocrine dysfunction, or dysfunction of any other organ;2) Allergy or hypersensitive reaction to remimazolam;3) Mental disorder;4) Recent respiratory infection (2 weeks);5) Other reasons that researchers hold as inappropriate for participation in this trial: under specialized care or living in social welfare institutions or any other factors that could affect their ability to participate in the study.

### Random and binding

Since inclusion and exclusion criteria are carefully designed to limit potential bias, simple randomization will be conducted. Randomization will be performed in a 1:1 ratio according to a computer-generated randomization table (SPSS Inc., Chicago, IL, United States) at the beginning of the study.

The research team will be divided into two independent cohorts: anesthesia implementation researchers and postoperative assessment researchers. Postoperative assessment researchers will not be involved in the implementation and management of anesthesia and be blinded to the study allocation. Unblinding will not be carried out until after the completion of the study when all data will have been entered and the statistical analysis plan will have been confirmed.

### Enrollment

Potential participants will be screened the day before the surgery by an independent researcher. The study protocol, potential risks, potential benefits, and alternatives will be explained to the children and their parents. Moreover, parents will be informed that the data would be analyzed anonymously and that no payment would be received for participation in the study. An independent researcher will be responsible for obtaining written informed consent and for the collection of demographic and baseline data from the participants.

### Intervention

#### Preoperative period

All children will be confirmed to meet the ASA fasting guideline. Demographic and baseline data will be obtained by a member of the research team. No premedication will be given before anesthesia. To mitigate preoperative anxiety and facilitate the completion of venipuncture before anesthesia induction, children will be allowed to watch cartoon videos in the presence of one of their parents or guardians. During the preoperative period, an independent researcher will assess the anxiety level by using the modified Yale Preoperative Anxiety Scale (m-YPAS, Supplementary Table S1).

#### Induction of anesthesia

Upon arriving at the operative area, children will be monitored with continuous electrocardiogram (ECG), heart rate (HR), respiratory rate (RR), pulse oxygen saturation (SpO_2_), and non-invasive blood pressure (NIBP). Those values will be recorded every 5 min.

The children will receive different anesthesia induction regimens based on their group allocation. 1) Remimazolam group: An intravenous administration of fentanyl (Yichang Humanwell Pharmaceutical Co., Ltd., China) at a dosage of 2–3 μg kg^-1^, remimazolam (Yichang Humanwell Pharmaceutical Co., Ltd., China) at 0.3–0.5 mg kg^-1^, and rocuronium (Siegfried Hameln GmbH, Germany) at 0.6 mg kg^-1^ will be given. 2) Sevoflurane group: Anesthesia will be induced with 8% sevoflurane (Maruishi Pharmaceutical Co. Ltd., Osaka, Japan) in 100% oxygen at a flow rate of 6 L min^-1^, followed by intravenous fentanyl at 2–3 μg kg^-1^ and rocuronium at 0.6 mg kg^-1^. Once adequate anesthetic depth is achieved, orotracheal intubation will be performed.

#### Maintenance of anesthesia

After intubation, pressure-controlled mechanical ventilation will be used to maintain the end-tidal carbon dioxide partial pressure (P_et_CO_2_) between 35 and 45 mmHg. 1) In the remimazolam group, remimazolam will be infused at an initial rate of 2 mg kg^-1^. h^-1^ (1–3 mg kg^-1^. h^-1^) and remifentanil (Yichang Humanwell Pharmaceutical Co., Ltd., China) will be administered at an initial infusion rate of 0.25 μg kg^-1^ min^-1^ (0.1–0.5 μg kg^-1^ min^-1^) (Fang et al., 2023). 2) In the sevoflurane group, anesthesia will be maintained at a minimum alveolar concentration (MAC) of 1.0–1.5, with remifentanil being infused at an initial rate of 0.25 μg kg^-1^ min^-1^ (0.1–0.5 μg kg^-1^ min^-1^). Fentanyl will be administered intravenously (0.5–1 μg kg^-1^) as needed when the heart rate exceeds the baseline by more than 20%. All anesthetic medications will be discontinued at the end of the procedure.

Following the induction of anesthesia, an intravenous dose of 0.15 mL kg^-1^ dexamethasone will be administered to prevent postoperative nausea and vomiting (PONV) (Czarnetzki et al., 2008). For postoperative analgesia, an intravenous dose of 1 mg kg^-1^ ketorolac tromethamine will be administered. After completing surgery, neuromuscular blockade will be reversed with neostigmine (0.02 mL kg^-1^) and atropine (0.01 mL kg^-1^). Subsequently, the intubation will be removed when the tidal volume will be ≥ 6 mL kg^-1^ and the frequency ≥ 15.

#### Recovery from anesthesia and follow-up

In the post-anesthesia care unit (PACU), the Pediatric Anesthesia Emergence Delirium (PAED) scale and the Face, Legs, Activity, Cry, and Consolability (FLACC) scale will be used to assess patients at 0, 5, 10, 20, and 30 min after emergence from anesthesia. Patients with pain (FLACC ≥4 and PAED score <10) will be treated with 0.5 μg/kg of fentanyl. In the case of ED (PAED score ≥10 but FLACC <4), initial comfort measures will have been taken. Initial comfort measures include the application of weighted blankets or the provision of gentle and sustained touch by a PACU nurse (Eull et al., 2022; Kim et al., 2024). If these are ineffective, 1 mg kg^-1^ propofol will be administered. If the patient experiences both emergence delirium and pain (PAED score ≥10 and FLACC score ≥4), pain management will be prioritized and then the final PAED score will be re-assessed after 5 min (Somaini et al., 2016). The recovery of the patients from sedation will be assessed after the procedure using the modified Aldrete score (Supplementary Table S2). When the modified Aldrete score reaches 9, the child will be permitted discharge from the PACU.

The behavior change will be scored using the post-hospitalization behavior questionnaire for ambulatory surgery (PHBQ-AS) through a telephone follow-up survey. The study follow-up will be performed at 3 days after surgery in order to avoid the influence of first 2 days’ agitation, significant pain, or nausea on questionnaire response (Lee-Archer et al., 2020).

### Outcomes

#### Primary outcome

The primary outcome will be the incidence of emergence delirium, which will be defined to the Pediatric Anesthesia Emergence Delirium scale (PAED, Supplementary Table S3) ≥10 (Yang et al., 2022). The PAED score will be documented by the same well-trained doctor who will be blinded to the allocation group. The PAED scale has been proved to be a reliable and valid measurement tool for children aged 1–17 years in a post-anesthesia setting (Daoud et al., 2014).

#### Secondary outcomes

The secondary outcomes will include the following:1) Extubation time: the time interval from the end of the surgery to extubation.2) Recovery time: the time interval from the end of the surgery to spontaneous eye opening in the PACU.3) The pain score will be assessed by the Face, Legs, Activity, Cry, and Consolability scale (FLACC, Supplementary Table S4). The FLACC scale has been proven to be a reliable instrument for assessing postoperative pain in children (from birth to 18 years) who have undergone outpatient surgery under general anesthesia (Crellin et al., 2015).4) The incidence of rescue propofol or fentanyl in the PACU.5) Behavior change will be assessed by the post-hospitalization behavior questionnaire for ambulatory surgery (PHBQ-AS, Supplementary Table S5) at 3 days. The PHBQ-AS has been validated in children aged 2–7 years (Lee-Archer et al., 2022).6) The satisfaction scores of the surgery doctor and attending anesthesiologist will be assessed after surgery by a 3-point scale: very satisfied, satisfied, and dissatisfied.7) Adverse events (AEs):i. Respiratory adverse events:a. Minor adverse events: oxygen desaturation (SpO_2_<90%), airway obstruction, coughing, or wheezing.b. Major adverse events: laryngospasm and bronchospasm.ii. Cardiovascular adverse events: hypotension (SBP <70 mmHg +2 times age) and bradycardia (HR < 70 beats. min^-1^).iii. Other adverse events: post-operative nausea, vomiting, etc.

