#### Sample size

The PAED score, which has excellent sensitivity (91%) and specificity (98%), will be used to assess emergence delirium (Janssen et al., 2011). A previous study showed that the rate of emergence delirium in pediatric tonsillectomy and adenoidectomy during sevoflurane anesthesia was approximately 44% (Yang et al., 2022). Hence, a sample size of 72 patients will provide 80% power at a 0.05 level of significance to detect a 30% difference in the proportion of children who attain emergence delirium in each group. Estimating a 20% drop out rate, 90 children will be needed in this study (PASS 15.0).

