### Statistical analysis

The statistical analysis will be based on the intention-to-treat principle, including all randomized patients, regardless of subsequent withdrawal or deviation from the protocol. The data will be analyzed by SPSS version 24.0 for Windows (SPSS Inc., Chicago, IL, United States). The normality of distribution of continuous variables will be tested by the one-sample Kolmogorov–Smirnov test. Continuous variables with normal distribution will be presented as the mean ± standard deviation (SD), while non-normal variables will be presented as the median (interquartile range). Continuous variables will be analyzed using the Student’s t-test or Mann–Whitney U test based on the distribution, and categorical variables will be analyzed by the chi-squared test or Fisher’s exact test. Since there is only one primary outcome and the secondary outcomes are considered exploratory, no subgroup analyses or any other additional analyses will be planned in this study. No corrections for multiplicity will be planned. All statistical tests are two-sided, and a *p*-value <0.05 will be considered significant.

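### The three-grade satisfaction scores are ordered, but the rule that most naturally covers them is chi-squared or Fisher's exact test, which ignores order; an ordered test would suit them better at almost no cost

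*Protocol article*

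**What the plan says.** In the protocol article, item 6 under Secondary outcomes lists the satisfaction of the surgeon and of the attending anesthesiologist, "assessed after surgery by a 3-point scale: very satisfied, satisfied, and dissatisfied". The article calls these scores.

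The Statistical analysis section gives two rules for comparing the groups:

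- "Continuous variables will be analyzed using the Student’s t-test or Mann–Whitney U test based on the distribution"
- "categorical variables will be analyzed by the chi-squared test or Fisher’s exact test"

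There is no separate rule for ordered categories, and no sentence says which rule applies to satisfaction. The same section says that "the secondary outcomes are considered exploratory" and that "All statistical tests are two-sided". No expected distribution, effect size or power is given for satisfaction. The section on randomization and blinding foresees a statistical analysis plan that is confirmed before unblinding; that plan is not at hand.

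**The concern.** The grades run from best to worst, and the natural question is whether raters are more satisfied in one arm than in the other. Pearson's chi-squared test on a 2 × 3 table has two degrees of freedom and gives the same p-value however the three columns are arranged. The extension of Fisher's exact test to that table also ignores the order. A rank or trend test puts its single degree of freedom on the ordered shift. If the shift is consistent along the scale, the nominal test is less likely to detect it.

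What is at stake is modest: some sensitivity for one exploratory outcome, and a choice between tests that is better fixed before the data are seen.

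**Working it through.** **1. Inputs.** From the protocol: 1:1 allocation; 90 children, so 90/2 = 45 per arm; 72 evaluable after a 20% loss, so 72/2 = 36 per arm; two-sided 5% level. Assumed: every satisfaction distribution and every effect size below.

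**2. The plan's own figure.** The protocol states no power for satisfaction, so only the primary sample size can be reproduced: "a sample size of 72 patients will provide 80% power at a 0.05 level of significance to detect a 30% difference". With 44% against 14%, the mean proportion is 0.29 and

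n per arm = [1.960·√(2·0.29·0.71) + 0.842·√(0.44·0.56 + 0.14·0.86)]² / 0.30² = (1.258 + 0.510)² / 0.09 ≈ 34.7, so 35.

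That is 70 in total against the stated 72. Power at 36 per arm is 81.5%, and 72/(1 − 0.20) = 90. The arm sizes used here are therefore the plan's own.

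**3. Large-sample comparison.** Suppose the whole effect lies along the ordering, so that both tests have the same noncentrality λ = (1.960 + z)², where z is the normal quantile of the ordered test's power.

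| Power, ordered test (1 df) | λ | Power, chi-squared (2 df) | Loss, points |
|---|---|---|---|
| 50% | 3.84 | 40.1% | 9.9 |
| 70% | 6.17 | 59.7% | 10.3 |
| 80% | 7.85 | 70.9% | 9.1 |
| 90% | 10.51 | 83.5% | 6.5 |

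**4. Simulation, uniform shift.** 40,000 trials per scenario compared Pearson chi-squared with the tie-corrected Mann–Whitney test. The shift multiplies the odds at both cut-points by the same odds ratio (OR). For example, with a baseline of 50/40/10% (*very satisfied* / *satisfied* / *dissatisfied*) and OR 2, the odds of 1 and 9 become 2 and 18, which gives 66.7/28.1/5.3%. Results for this baseline at 45 per arm:

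| OR | Chi-squared | Mann–Whitney | Gain, points |
|---|---|---|---|
| 1.5 | 12% | 16% | 4 |
| 2 | 29% | 38% | 9 |
| 2.5 | 46% | 57% | 11 |
| 3 | 60% | 71% | 11 |
| 4 | 79% | 87% | 8 |

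Across five baselines and both arm sizes the gain was about 3–4 points at OR 1.5, 8–9 at OR 2, 10–11 at OR 2.5, 10–12 at OR 3 and 6–12 at OR 4.

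**5. Simulation, other shifts in one direction, 45 per arm.**

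| Arms compared | Chi-squared | Mann–Whitney |
|---|---|---|
| 50/40/10 v 70/25/5 | 40% | 50% |
| 40/40/20 v 60/30/10 | 41% | 51% |
| 60/35/5 v 80/18/2 | 44% | 56% |
| 65/34/1 v 85/14.5/0.5 | 56% | 60% |

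The last row is a nearly binary scale; there the gain falls to about 4–5 points across the two arm sizes.

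**6. Simulation, non-uniform shifts, 45 per arm.**

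| Arms compared | Chi-squared | Mann–Whitney | Change, points |
|---|---|---|---|
| 50/30/20 v 70/25/5 | 59% | 61% | +2 |
| 30/60/10 v 60/30/10 | 78% | 69% | −9 |
| 40/40/20 v 60/20/20 | 49% | 30% | −19 |
| 60/20/20 v 50/45/5 | 79% | 6% | −73 |

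**7. Validity and the Fisher branch.** With no difference between arms, both tests rejected in about 5% of trials or somewhat fewer. If *dissatisfied* is 10%, its expected count is 0.10 × 45 = 4.5 per arm, or 3.6 at 36 per arm. With 5–10% *dissatisfied*, 59–97% of simulated null trials had an expected count below 5. Fisher's exact test would then often be the one used. The power figures above are for Pearson chi-squared, not for Fisher.

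**The case against.** The strongest reply is that this is a preference between two valid tests for an outcome declared exploratory. The protocol does not assign satisfaction to the categorical rule. It calls the grades scores, it already names the Mann–Whitney test, and it foresees an analysis plan that may settle the matter. That stands in part: the assignment is an inference, though reading three verbal grades as a continuous variable would be the less natural course.

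A reader might go further and infer that the plan throws away about 10 points of power for nothing. The documents do not support this. They give no satisfaction distribution or effect, so any figure is conditional. The nominal test also buys something, namely sensitivity to patterns that are not a uniform shift. Two of the reversals in step 6, where *very satisfied* rises by 20 or 30 points and *dissatisfied* does not move, are not far-fetched. The largest reversal has little overall direction, so it says less about the question a satisfaction score is meant to answer.

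A reader might also infer that chi-squared leaves the trial unable to say which arm did better. That is too strong: the direction can be read from the counts per grade. What the nominal test lacks is a p-value aimed at that direction.

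Finally, the simulated chi-squared powers do not describe the Fisher branch. This limits the precision of the figures, not the principle, because Fisher's test ignores the order too.

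**Conclusion.** The point holds as a minor improvement, not as an error. The scale is ordered, and the rule that most naturally covers it does not use the order. For a consistent shift toward greater satisfaction, an ordered test gains roughly 3 to 12 points of power at 36 to 45 per arm: about 3–4 for small effects, about 4–5 if *dissatisfied* is about 1%, and about 8–12 for odds ratios of 2 to 3. This rests on assumed distributions, on a shift that is close to uniform, and on Pearson chi-squared as the comparator. With a non-uniform shift the ordered test can have less power. Nothing here touches the primary outcome, the sample size or the validity of the stated tests.

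**What to change.** Add one sentence to the Statistical analysis section: the surgeon and anesthesiologist satisfaction scores, being ordered, will be compared between groups with the tie-corrected Mann–Whitney U test (or the linear-by-linear trend test), and the counts in each grade will be shown by arm. Name one of the two tests, and do so before unblinding, so that the choice does not depend on the data. If the analysis plan already says this, aligning the protocol text is enough.

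The cost is one sentence. No new data are needed, and the Mann–Whitney test is already in the plan. The price is lower power for patterns that are not a uniform shift; the counts per grade would let a reader see such a pattern.
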